### 3-dimensional LA voltage map for lesion assessment

The first 25 patients in each intervention group will undergo postablation electroanatomic mapping (EAM) of the LA using a 3 dimensional EAM system (RHYTHMIA; Boston Scientific) to quantify the proportion of isolated PVs, the proportion of isolated carinas and the lesion size. A dedicated high-resolution mapping catheter (Orion; Boston Scientific) will be introduced to create a high-density voltage map of the LA using the FlexCath or FARADRIVE sheath already present.

Given that the workflow tested in our study is PFA/cryoballoon procedures guided by fluoroscopy only without the use of a 3-dimensional (3D) mapping system, the acute endpoint of the procedure will be assessed before the beginning of the 3D mapping part. In case a reconnected PV is observed during 3D-EAM, no additional ablation is allowed because it would bias the overall study.

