### Postablation follow-up

Blood sampling for postablation high-sensitive troponin release is obtained in the morning of the first postablation day.

Antiarrhythmic drugs are allowed during the first 3 months (blanking period) but will be discontinued after 3 months by the latest. Following discharge, daily automatic ICM data transmissions will be used to assess and record atrial tachyarrhythmia events and burden. Additionally, manual transmissions are performed once weekly. Clinical follow-up visits occur at 3, 6, 12, 24, and 36 months at the study center enrolling the patient or by external cardiologists. Telephone follow-ups are conducted at 3 months ± 2 weeks, 12 ± 2 months, 24 ± 2 months, and 36 ± 2 months to assess hospital or emergency room admissions, electrical cardioversions, repeat ablation procedures, stroke/transient ischemic attack, or death. During the 3-month telephone follow-up, a final evaluation of delayed procedural complications contributing to the safety endpoint is conducted. The 36-month telephone follow-up is the last follow-up. Quality-of-life (QoL) questionnaires are sent to patients by mail after 3 and 12 months to monitor QoL progression postablation by the EQ-5D-5L questionnaire.^28^ Refer to Table 2 for a summary of the enrollment, interventions, and assessments schedule.

**Table 2 tbl2:** Schedule of enrollment, interventions, and assessments

	Enrollment	Procedure		Follow-up			
	≥1 d prior to ablation	0	Hospital DC	3 mo	12 mo	24 mo	36 mo
Eligibility screen	X						
Informed consent	X						
Clinical examination	(X)		(X)				
Laboratory investigation	(X)		(X)				
12-lead ECG	(X)		(X)				
Echocardiography	(X)						
QoL questionnaire	X			X	X		
Cardiac CT or MRI	(X)						
PV isolation		(X)					
3D-EAM (substudy)		X∗					
ICM implantation		X					
ICM data transmission							
Telephone call				X	X	X	X
Safety endpoint assessment			X	X			
Primary endpoint assessment					X		

In parentheses are routine assessments and interventions (not study specific).

3D = 3-dimensional; CT = computed tomography; DC = discharge; EAM = electroanatomic mapping; ECG = electrocardiogram; ICM = implantable cardiac monitor; MRI = magnetic resonance imaging; PV = pulmonary vein; QoL = quality of life.

∗ Performed only in the first 25 patients in each intervention group.

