### Secondary endpoints

The procedural safety endpoint is a composite of (1) cardiac tamponade requiring pericardiocentesis, (2) persistent phrenic nerve palsy lasting >24 hours, (3) serious vascular complications requiring intervention, (4) stroke/transient ischemic attack, (5) atrioesophageal fistula, or (6) death. The safety endpoint is assessed during catheter ablation, the time until discharge, and the following 30 days. Information on safety events are collected throughout the trial by the investigators or their designees. All primary safety events will be reviewed and adjudicated by the clinical events committee members.

Other key secondary endpoints include (1) procedure duration, LA indwelling, and fluoroscopy times; (2) proportion of isolated PVs and carinas between the PVs in postablation 3D-EAM (only the first 25 patients in each study group); (3) AF burden; (4) proportion of patients with recurrence of any atrial tachyarrhythmia between days 0 and 90 postablation (blanking period); (5) proportion of patients undergoing a repeat ablation; (6) QoL changes at 3 and 12 months compared with baseline; and (7) modified analysis of the primary endpoint using a blanking period duration of 2 months as proposed in the recently renewed AF ablation consensus document.^30^ All secondary procedural and follow-up endpoints are listed in the Supplemental Table 3.

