### Statistical analysis

A statistician, who is blinded to treatment allocation, will perform analyses. The principal investigators will have full access to the data and will vouch for the data and the analysis. Analyses are conducted according to the intention-to-treat principle meaning that patients are analyzed based on the treatment arm to which they were originally allocated. The primary analysis is in the per-protocol population with confirmatory testing in all the randomized patients, in both these populations using the intention-to-treat principle. Hence, noninferiority will only be claimed for the FARAPULSE PFA catheter if the analysis in both populations show that the upper limit of the confidence interval of the rate ratio using Mantel-Cox time to first recurrence of any atrial tachyarrhythmia between days 91 and 365 postablation comparing FARAPULSE vs Arctic Front does not cross 20% (rate ratio of 1.2), using a 1-sided test with alpha of 5%.

The per-protocol population is defined as all patients in which (1) the randomized device was used to initiate the ablation (irrespective of whether this ablation was completed successfully, or whether a second device was used to complete the ablation) and (2) none of the inclusion and exclusion criteria were breached.

Primary analysis will take place after all patients have completed 1-year follow-up. For the primary analyses (FARAPULSE vs Arctic Front), unadjusted survival curves are estimated by the Kaplan-Meier method and compared by log rank tests. Unadjusted rate ratios and confidence intervals for rate ratios are derived from Mantel-Cox models. The proportional hazards assumption is assessed by visual inspection of the log-negative-log plot and through a formal test of the interaction term group × time at an alpha of 0.05. Secondary endpoints expressed as time to event are analyzed similarly using Kaplan-Meier survival curves and a log-rank test. All tests are conducted at an alpha level of 0.05. Basic assumptions are verified prior to analysis. In case of noninferiority for the primary endpoint, a superiority analysis is performed using a 2-tailed significance alpha level of 0.05.

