Comparisons between the 2 treatment groups are performed using demographic, clinical, procedural, and imaging characteristics, and tested if postrandomization. Continuous variables are presented as mean ± SD or median and interquartile range depending on their distribution. Categorical variables are stated as number and proportion. Characteristics are compared between the 2 treatment groups by means of unpaired *t* tests for continuous variables and chi-square tests or Fisher’s exact tests for categorical variables and reported *P* values will be 2-sided. If a normal distribution cannot be assumed, nonparametric tests are considered to compare patient characteristics.

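### If the generic chi-square or Fisher test is applied per vein in the mapping substudy it ignores clustering within patients; adjusting QoL for the enrollment score would be a free gain in precision

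*Protocol article*

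**What the plan says.** The Statistical analysis section gives two rules that could apply to secondary endpoints.

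- Time to event: "Secondary endpoints expressed as time to event are analyzed similarly using Kaplan-Meier survival curves and a log-rank test".
- Everything else: "Comparisons between the 2 treatment groups are performed using demographic, clinical, procedural, and imaging characteristics, and tested if postrandomization". The methods are unpaired t "tests for continuous variables and chi-square tests" or Fisher's exact tests, with nonparametric tests if normality cannot be assumed. P values are two-sided, and "All tests are conducted at an alpha level of 0.05".

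The Secondary endpoints section lists, among the key ones, the "proportion of isolated PVs and carinas between the PVs in postablation 3D-EAM (only the first 25 patients in each study group") and "QoL changes at 3 and 12 months compared with baseline".

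The section on the 3-dimensional LA voltage map says that mapping is done "to quantify the proportion of isolated PVs, the proportion of isolated carinas and the lesion size". It does not say whether the proportion is taken over all veins in a group or within each patient.

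The Postablation follow-up section says that questionnaires are sent at 3 and 12 months "to monitor QoL progression postablation by the EQ-5D-5L questionnaire". Table 2 also marks the questionnaire at enrollment, so a baseline score is available.

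**The concern.** **Mapping endpoint.** Postablation mapping is postrandomization imaging, so the generic rule plausibly governs it, and the time-to-event rule cannot. A proportion of isolated veins invites a 2 × 2 table of veins. Several veins come from one patient, treated in one procedure with one device, so their outcomes are likely to be correlated. Chi-square and Fisher tests assume independence. Positive correlation makes the standard error too small and the p value too optimistic, in the substudy that gives the trial's direct evidence on lesion formation.

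**QoL endpoint.** The only test the article offers for a continuous outcome is the unpaired t test or a nonparametric equivalent, with no mention of baseline adjustment. A change score uses the baseline by subtraction, but less efficiently than regression on it. What is at stake here is precision, not validity.

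**Working it through.** The article states no effect size, power or expected rate for either endpoint, so there is no figure of its own to reproduce.

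**(a) Veins**

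From the article: 25 patients per group, two-sided alpha 0.05. Assumed, because not stated: m = 4 veins per patient (25 × 4 = 100 per group), within-patient correlation (ICC) 0.1 to 0.3, true isolation 70 to 98%.

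Design effect: DE = 1 + (m − 1) × ICC. Large-sample size of a naive nominal 5% test: 2 × [1 − Φ(1.96/√DE)]. Effective number of veins per group: 100/DE.

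| ICC | DE | Naive SE too small by factor | Effective veins per group | True size |
|---|---|---|---|---|
| 0.1 | 1.3 | 1.14 | 77 | 8.6% |
| 0.2 | 1.6 | 1.26 | 62 | 12.1% |
| 0.3 | 1.9 | 1.38 | 53 | 15.5% |

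The formula ignores discreteness, which matters for Fisher's test and near complete isolation. A beta-binomial simulation under the null (25 patients per group, 4 veins each, 20,000 runs per setting) gives these rejection rates, as chi-square / Fisher / t test on the number of isolated veins per patient:

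| True isolation | ICC 0 | ICC 0.1 | ICC 0.2 | ICC 0.3 |
|---|---|---|---|---|
| 70% | 5.2 / 3.6 / 5.0% | 8.6 / 6.4 / 4.9% | 12.0 / 9.3 / 4.8% | 16.0 / 12.8 / 4.9% |
| 90% | 5.2 / 2.8 / 5.1% | 8.8 / 5.5 / 4.9% | 12.3 / 8.2 / 4.6% | 16.0 / 11.3 / 4.6% |
| 95% | 4.4 / 2.1 / 5.1% | 7.7 / 4.2 / 4.7% | 11.5 / 6.9 / 4.6% | 14.5 / 9.0 / 3.7% |
| 98% | 3.8 / 0.5 / 3.6% | 6.6 / 1.4 / 2.4% | 9.2 / 2.6 / 1.6% | 11.8 / 3.9 / 0.8% |

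Chi-square exceeds 5% at every isolation rate shown once ICC reaches 0.1. Fisher exceeds 5% at 70 and 90% isolation from ICC 0.1 and at 95% from ICC 0.2; at 98% it does not exceed 5% up to ICC 0.3. The patient-level test does not exceed its nominal level beyond simulation error, but becomes conservative near the ceiling.

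Fewer units per patient means less inflation. With m = 2, DE = 1 + ICC, which is 1.1 to 1.3 over the same ICC range.

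**(b) QoL**

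Assumed: equal variance σ² at baseline and follow-up, correlation ρ of 0.3 to 0.7.

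- Variance of change: 2σ²(1 − ρ).
- Residual variance after adjustment for baseline: σ²(1 − ρ²).
- Ratio: (1 − ρ²)/[2(1 − ρ)] = (1 + ρ)/2.

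| ρ | Variance ratio | Patients giving ANCOVA the precision of the change test in 210 | ANCOVA power where the change test has 80% |
|---|---|---|---|
| 0.3 | 0.65 | 210 × 0.65 → 137 | 93.5% |
| 0.5 | 0.75 | 210 × 0.75 → 158 | 89.9% |
| 0.7 | 0.85 | 210 × 0.85 → 179 | 86.0% |

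Power is Φ[(1.96 + 0.84)/√ratio − 1.96]. The simulated type I error of the t test on change (99 per group) was 4.9 to 5.0% at each ρ, so that test is valid.

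**The case against.** The strongest reply is that the article assigns these tests to neither endpoint. The generic rule speaks of characteristics and ends on patient characteristics; QoL is never paired with a test. The model for a secondary endpoint is commonly left to an analysis plan, which is not at hand, and neither is the supplement listing all secondary endpoints.

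Much of this stands. A reader might infer that the plan commits to a vein-level chi-square test and to a QoL test that ignores baseline. The article supports neither inference:

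- The unit for isolation is not named. A proportion of isolated veins can be computed within each patient, or reduced to all veins isolated yes or no. The generic tests would then be free of the clustering problem.
- No QoL test is stated, and the endpoint, being a change, already uses the baseline score. The t test on change would not be an error.
- A single inflated error rate for chi-square and Fisher together would be wrong, because Fisher inflates less and may not inflate at all near complete isolation. That setting is plausible for veins: isolation is verified, with further applications or freezes where needed, before mapping starts. It carries over less readily to carinas, whose isolation is not a stated procedural endpoint.

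What the reply does not remove is that the article does state a method for postrandomization imaging data, and that this method is unsafe under one natural reading of the mapping endpoint. Leaving the unit open is what allows that reading.

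**Conclusion.** The point holds as a low-cost improvement in two parts of unequal weight.

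(a) Conditional on a vein-level analysis, the stated tests do not allow for within-patient correlation. With 4 veins per patient, ICC 0.1 to 0.3 and 90% isolation, the true error of a nominal 5% test is about 9 to 16% for chi-square and 5.5 to 11% for Fisher. At 98% isolation Fisher remains at 1.4 to 3.9% over the same ICCs, while chi-square is at 6.6 to 11.8%. The number of veins, the ICC and the isolation rate are all assumptions.

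(b) Baseline adjustment of QoL is an efficiency gain only: 15 to 35% less variance than a change-score t test if ρ lies between 0.3 and 0.7 and the variances are equal.

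Neither part touches the sample size, the noninferiority decision or any figure in the article.

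**What to change.** **Mapping.** State the unit of analysis. Either take the patient as unit (number of veins or carinas isolated, or all isolated yes/no), or analyze per vein with a logistic GEE or mixed model clustered on patient. With 25 patients per group, a GEE should use a small-sample correction to its standard errors. If isolation is nearly complete, the patient-level summary is the simpler choice, although the t test on counts is then conservative. The cost is somewhat wider, honest intervals compared with a naive vein-level test.

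**QoL.** Compare EQ-5D-5L at 3 and 12 months by ANCOVA, or a repeated-measures model, with the enrollment score as covariate. The score is already collected, so the cost is one sentence.

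Neither change needs new data, visits or patients. Both should be fixed before the data are analyzed. If the analysis plan already does this, the article's generic wording needs only a clause to say so.

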### Ethical considerations

The local ethical committees (2022-D0024) have approved this study. The trial will be conducted in accordance with the principles of Good Clinical Practice and the Declaration of Helsinki.

Participation in the study assumes that patients have already committed to undergoing catheter ablation for paroxysmal AF. The catheter ablation procedure employed in this trial mirrors the established treatment approach for AF and is not experimental. Consequently, the risks associated with participation are equivalent to those of conventional AF ablation and remain unaffected by trial enrollment.

## Discussion

The SINGLE SHOT CHAMPION study is the first randomized controlled trial with blinded ICM based endpoint adjudication to compare the novel PFA modality (FARAPULSE) with the currently well-established cryoballoon ablation (Arctic Front) for PVI in patients with paroxysmal AF.

Single-shot approaches for PVI offer multiple advantages compared with point-by-point radiofrequency ablation including shorter learning curve and procedure times.^31^ The Arctic Front cryoballoon is now the most frequent used single-shot device. However, procedure-related complications associated to nonselective, thermal energy ablation such as atrioesophageal fistula and persisting phrenic nerve palsy occur.^9^ The novel FARAPULSE PFA system delivering high-voltage electrical fields potentially minimizes these risks by selective myocardial tissue ablation. Nevertheless, the first large postmarket registry (n = 1817 patients) reported occurrence of transient (n = 6) and even persistent (n = 1) phrenic nerve palsy after PVI with the FARAPULSE PFA system but no atrioesophageal fistula.^17^

The recently published, first randomized controlled ADVENT study (Pulsed Field or Conventional Thermal Ablation for Paroxysmal Atrial Fibrillation) comparing PFA and thermal ablation (cryoballoon and radiofrequency ablation) for PVI showed similar efficacy between both groups.^20^ One main limitation of this study may be the lack of continuous rhythm monitoring, possibly leading to underestimation of recurrence rates and AF burden. SINGLE SHOT CHAMPION addresses this limitation by providing continuous rhythm monitoring during follow-up via ICM in all participants. As shown previously, the choice of an adequate monitoring strategy is crucial for a reliable comparison of long-term efficacy between ablation technologies.^24^

## Conclusion

The SINGLE SHOT CHAMPION study is the first randomized controlled, multicenter study comparing the safety and long-term efficacy of the novel FARAPULSE PFA catheter with the standard-of-practice Arctic Front cryoballoon using ICM based follow-up data. It will contribute to a deeper understanding of the clinical performance and safety of the 2 systems and inform future selection of the optimal catheter ablation system in AF patients.
